### Sample size consideration

A population of 410 patients (205 in each arm) will be included in the study. The number of subjects necessary was calculated to show a difference in systolic blood pressure of 5 mmHg between the group with optimized follow up and the group with typical follow up, with an alpha risk of 5% and a beta risk of 20%. The variance in systolic blood pressure (18 mmHg) was calculated in the first 45 patients included in the study, in whom mean systolic blood pressure was 139.9 mmHg. The choice of the expected difference was justified by three reasons. First, there is a link between increase in blood pressure and the risk of stroke. Second, the Prediva study showed recently that a 2-mmHg decrease in blood pressure was unable to impact cognitive morbidity in the general population [32]. Third, with a 5-mmHg decrease in blood pressure, mean blood pressure should reach 135 mmHg, a level that is recommended in the guidelines and is in good accordance with a previous study [28].

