### Primary outcome

Systolic and diastolic blood pressure will be measured at the 6-month, 1-year and 2-year visits, by a nurse blinded to the randomization. The main assessment criterion will be systolic blood pressure measured after the first year of follow up, offering a compromise between the feedback from 1 year, allowing long-term evaluation of the benefit of the optimized follow up by the pair and minimizing the risk of losing track, in the case of an evaluation after 2 years. Blood pressure will be measured by nursing personnel who do not know the group into which the patient has been randomized.

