### Analysis strategy

Data will be analyzed by an analysis committee that will be blind to the groups studied, which will be called Groups A and B during the analysis. The assessment criteria will be expressed as quantitative values (mean and standard deviation) or as qualitative values (percentage). The variables expressed quantitatively will be blood pressure (systolic, diastolic, mean), glycosylated hemoglobin concentration, concentration of the various lipid parameters and scores on different scales (Rankin, MoCA, EQ-5D). The variables expressed qualitatively will be mortality rate, percentage of patients having another stroke, percentage of patients having blood pressure below the limit set by international guidelines, percentage of patients with normal glycosylated hemoglobin, percentage of patients with LDL cholesterol below 1 g/L and percentage of patients having a cognitive disorder (MoCA score <26). Quantitative data will be compared between the two groups using analysis of variance, with post-hoc analysis using Fisher’s least significant difference test in Prism (PLSD). Qualitative data will be compared between the two groups based on the chi-squared test and calculation of odds ratios. Sub-group analyses will be planned secondarily, depending on the cause of the stroke or depending on the patient’s cognitive state.

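### The 410 patients are exactly the evaluable number for 80% power, so the stated beta risk holds only with essentially complete 12-month readings; the 18 mmHg labelled a variance is a standard deviation

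*Protocol article*

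**What the plan says.** All the planning figures are in the protocol article under Sample size consideration. The enrolment figure is "A population of 410 patients (205 in each arm) will be included in the study". The target is given as "The number of subjects necessary was calculated to show a difference in systolic blood pressure of 5 mmHg" between the arms, "with an alpha risk of 5% and a beta risk of 20" per cent. The spread is described in these words: "The variance in systolic blood pressure (18 mmHg) was calculated in the first 45 patients included in the study".

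Under Primary outcome, the endpoint is fixed: "The main assessment criterion will be systolic blood pressure measured after the first year of follow up". One reason given for preferring one year to two is "minimizing the risk of losing track, in the case of an evaluation after 2 years". Under Analysis strategy, "Quantitative data will be compared between the two groups using analysis of variance", with no covariate named. The same section lists deaths among the outcomes: "The variables expressed qualitatively will be mortality rate, percentage of patients having another stroke". No rate of loss, death or missing readings appears anywhere in the article.

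**The concern.** A sample size formula returns the number of patients who contribute an outcome. The article applies its figure to the number of patients included. If the two are equal, each patient without a 12-month systolic reading takes power below the declared 80%. The article's own reasoning implies that some patients will have no reading: the choice of one year reduces the risk of loss without removing it, and patients who die before 12 months have no reading.

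What is at stake is the accuracy of the stated operating characteristics. Readers would take the trial to have 80% power for 5 mmHg when its actual power is somewhat lower. A separate matter in the same paragraph is that the spread carries the wrong statistical name, so the calculation cannot be reproduced from the words as printed.

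**Working it through.** **Inputs.** From Sample size consideration: difference 5 mmHg, spread 18 mmHg, alpha 5%, power 80%, 205 per arm. Sidedness is not stated; two-sided is taken because it reproduces the figure and fits a comparison by analysis of variance. The loss rates below are assumptions, applied equally to both arms.

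**Step 1: reproduce the plan's figure.** Reading 18 as a standard deviation, the normal approximation is

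n per arm = 2 × (1.960 + 0.842)² × 18² / 5² = 203.4, rounded up to 204 (408 in total).

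The exact two-sample t-test (noncentral t) needs 204.4, rounded up to 205 (410 in total). Its power is 79.9% at 204 per arm and 80.1% at 205. The published 410 is matched exactly, with less than one patient per arm to spare: 1 − 204.4/205 is about 0.3%.

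**Step 2: test other readings of the inputs.**
- 18 as a true variance: 2 × (1.960 + 0.842)² × 18 / 5² = 11.3, or 13 per arm by the t-test. This does not give 410, and a variance would not be in mmHg.
- One-sided 5% test: 161 per arm, 322 in total. This does not give 410.

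So 18 mmHg is a standard deviation, the test is two-sided, and no allowance for loss can be contained in 410.

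**Step 3: power when some readings are missing.** With loss proportion d, evaluable n per arm = 205 × (1 − d), the standard error of the difference is 18 × √(2/n), and power comes from the noncentral t with noncentrality 5 / SE. The last column is the difference detectable with 80% power.

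| Assumed loss | Evaluable per arm | SE (mmHg) | Power at 5 mmHg | Detectable difference |
|---|---|---|---|---|
| 0% | 205 | 1.78 | 80.1% | 5.0 mmHg |
| 5% | 194.75 | 1.82 | 78.1% | 5.1 mmHg |
| 10% | 184.5 | 1.87 | 75.8% | 5.3 mmHg |
| 15% | 174.25 | 1.93 | 73.4% | 5.4 mmHg |
| 20% | 164 | 1.99 | 70.8% | 5.6 mmHg |

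**Step 4: what baseline adjustment could return.** Adjusting for baseline systolic pressure with baseline-to-12-month correlation r reduces the residual standard deviation to 18 × √(1 − r²): 17.2 mmHg at r = 0.3 and 15.6 mmHg at r = 0.5. The article gives no correlation, so both values are assumptions. Power from the same noncentral t:
- 10% loss: 79.7% at r = 0.3; 86.7% at r = 0.5.
- 20% loss: 74.8% at r = 0.3; 82.5% at r = 0.5.

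Adjustment therefore offsets the loss for some combinations of loss and correlation and not for others.

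**The case against.** The strongest reply is that the calculation itself contains no error: the stated inputs give 410. What is missing is an allowance, and the size of its effect rests wholly on loss rates that the article does not supply. Several design features should keep loss low. Patients must be able to go home at once or after less than one month of rehabilitation, a caregiver must agree to two years of follow up, both arms have consultations at 6 and 12 months, and one year was chosen partly to limit loss. The section on optimized follow up also provides for collecting information after a patient discontinues. A shortfall of 2 to 4 points introduces no bias and leaves the type I error unchanged, and a null result will be read from its confidence interval whatever power was planned.

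Most of this stands, and it sets the weight of the point. It does not remove it. Because the inputs reproduce 410 exactly, this is not an inference from the brevity of an article: a fuller document could name a loss rate, but could not make 410 enrolled and 80% power both true for this unadjusted two-sided test once loss exceeds about 0.3%.

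Four stronger readings are tempting, and the documents do not support them:
- *The trial is seriously underpowered.* That would need losses of 15 to 20%, and nothing in the article indicates such rates.
- *The wrong term puts the sample size in doubt.* The unit and the reproduced figure both show a standard deviation; the slip does not affect 410.
- *A standard deviation from 45 patients, at an unnamed visit, is a defect in itself.* Sampling error in a planning value is universal and runs in both directions, and the visit is a detail that an article may leave to the full protocol.
- *Baseline adjustment would make good the loss.* It may, but only at a sufficient correlation, and the analysis described names no covariate.

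**Conclusion.** The point holds in a limited form. The 410 patients to be included are the evaluable number for 5 mmHg, standard deviation 18 mmHg, two-sided alpha 5% and 80% power, with no reserve. The declared beta risk of 20% is met only with essentially complete 12-month systolic readings, while the article itself acknowledges possible loss and expects some deaths.

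The size is conditional on assumed loss: about 2 points of power at 5%, 4 points at 10% and 9 points at 20%. These figures assume equal loss in the two arms, an unadjusted comparison and a true standard deviation of 18 mmHg. The mislabelled variance is a plain wording error with no numerical consequence. The point is worth correcting because the correction is cheap, and it ranks below must-fix.

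**What to change.** Keep 410 and amend the sample size paragraph:

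1. State the expected 12-month loss (deaths, withdrawals and missed readings together), the evaluable number that results, and the power that follows for the comparison as planned. For example, 10% loss leaves 410 × 0.9 = 369 evaluable patients and about 76% power.
2. Replace the term variance by standard deviation for the 18 mmHg.
3. If a baseline-adjusted analysis is adopted, show its power as well, conditional on a stated baseline-to-12-month correlation. Do not present it as a general remedy.

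The cost is a few sentences and a slightly less favourable stated power. No extra patients are needed, and the endpoint and trial conduct do not change.

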### Analysis strategy

Data will be analyzed by an analysis committee that will be blind to the groups studied, which will be called Groups A and B during the analysis. The assessment criteria will be expressed as quantitative values (mean and standard deviation) or as qualitative values (percentage). The variables expressed quantitatively will be blood pressure (systolic, diastolic, mean), glycosylated hemoglobin concentration, concentration of the various lipid parameters and scores on different scales (Rankin, MoCA, EQ-5D). The variables expressed qualitatively will be mortality rate, percentage of patients having another stroke, percentage of patients having blood pressure below the limit set by international guidelines, percentage of patients with normal glycosylated hemoglobin, percentage of patients with LDL cholesterol below 1 g/L and percentage of patients having a cognitive disorder (MoCA score <26). Quantitative data will be compared between the two groups using analysis of variance, with post-hoc analysis using Fisher’s least significant difference test in Prism (PLSD). Qualitative data will be compared between the two groups based on the chi-squared test and calculation of odds ratios. Sub-group analyses will be planned secondarily, depending on the cause of the stroke or depending on the patient’s cognitive state.

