### Participant eligibility

Patients over the age of 40 years are included, who have had a first transient or permanent, ischemic or hemorrhagic stroke, regardless of the cause, who have high blood pressure and have not had sequelae justifying long-term management in a rehabilitation center. The existence of other risk factors (diabetes mellitus, lipid disorders) is not a criterion for exclusion. The patients included must have a member of their social circle who agrees to invest 2 years in following up on the patient, in association with the assigned nursing personnel, even if they are in the end randomized to the group that will have typical follow up, in order to avoid selection bias. The complete inclusion and exclusion criteria are described in Table 1.

**Table 1 Tab1:** Population criteria

*Inclusion criteria*
○ Patients over 40 years of age ○ Patients who have had a first stroke, transient or permanent, ischemic or hemorrhagic, justifying hospitalization ○ Patients with high blood pressure already treated or discovered at the time of the stroke and justifying the start of treatment ○ Patients who have had a stroke with sequelae allowing immediate return home or justifying a stay of less than 1 month in rehabilitation ○ Patient having a member of his social circle who has agreed to provide follow up for 2 years in association with the assigned nursing personnel in case of randomization into the “optimized follow up” group
*Exclusion criteria*
○ Patients below 40 years of age ○ Patients with a history of stroke ○ Patients who do not have high blood pressure discovered by treatment prior to the stroke or by abnormal blood pressure during hospitalization ○ Patients who have had a stroke causing serious sequelae, justifying an extended stay in a rehabilitation department ○ Patient who has no one in their social circle capable of working with the assigned nursing personnel, or patient living in an institution

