**Fig. 2 Fig2:**
[figure not shown]
Schedule of enrollment, interventions, and assessments

The study will be presented at the time of an interview with the nursing personnel from the department assigned to the CEOPS study, in the presence of the doctor from the department, and a family member/friend likely to participate in the optimized follow up will be identified. The family member/friend is chosen on a voluntary basis, on the ability to understand and follow the different aspects of the recommendations, and on the proximity to the patient. After a period of consideration, the patient and the caregiving family member/friend will give their consent to participate in the study. Patients will be randomized into two groups, “optimized follow up” or “typical follow up.” Before being discharged, the two training sessions for the patient and the caregiving family member/friend will be given by the nursing personnel assigned to the CEOPS study. A letter of information will be sent to the attending physician and, possibly, to the other specialist physicians involved in the patient’s management (cardiologist, diabetologist, etc.). Before being discharged, blood pressure, the abdominal perimeter, glycosylated hemoglobin, plasma concentrations of the various lipids, coagulation parameters, the Rankin score, the quality of life scale and the Montreal Cognitive Assessment (MoCA) scale will be measured. The treatment upon discharge will be assembled.

In both groups, the patient and the family member/friend involved in the CEOPS study will be asked to fill out a follow-up notebook, where the following are to be noted: monitoring of blood pressure and various examinations performed, all the para-clinical examinations and consultations the patient has had, the adverse effects observed and the inter-current events. At each consultation, a report will be sent to the attending physician to keep the physician informed of the conclusions of the medical consultation. The nursing personnel assigned to the CEOPS study can at any time call on the physician in the department handling the patient’s follow up to inform the attending physician of the need for a change in treatment if it is found that the risk factors are not being properly monitored. One last information session will provide encouragement to the family member/friend to continue to be involved in the patient’s follow up in order to continue optimal monitoring of the risk factors and the treatment.

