### Secondary outcomes

Several secondary endpoints will be recorded at the different visits: glycosylated hemoglobin at 6 months, 1 year and 2 years to assess glucose metabolism; the plasma lipid parameters (total cholesterol, low-density lipoprotein (LDL) cholesterol, high-density lipoproteins (HDL) cholesterol and triglycerides); anticoagulant treatment monitoring, if relevant; waist circumference; therapeutic compliance (8-item Morisky scale); mortality; occurrence of a new stroke or myocardial infarction; and occurrence of adverse effects from medications (with validation by a regional drug monitoring center). Functional disability will be assessed by the Rankin score, cognitive state by the MoCA scale and quality of life by the Euroqol 5-Dimension (EQ-5D) questionnaire. The medico-economic impact will be assessed by a specific questionnaire filled out by the caregiver, with information on number of consultations (general practitioner, specialized consultations), home nurse time, physiotherapy consultation, number of para-clinical examinations, number of hospitalizations, professional inability, assignment of loss of autonomy (housekeeper, help with personal hygiene, medical device) and remote alarm. The analysis will be also based on an estimation of time spent by the caregiver (personal time, professional impact) and the impact on the caregiver’s own health status.

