The purpose of the study is to lower the morbidity/mortality, which may follow the onset of a first stroke, using optimized follow up. Considering the complexity of the morbidity/mortality criterion and the necessary feasibility criterion in terms of the number of subjects needed, the choice of the main assessment criterion, blood pressure, offers the dual advantage of being strongly correlated with risk in terms of morbidity/mortality and of being a relevant criterion in nursing care. Nevertheless, the results obtained in the Prediva study prompted us to consider a greater decrease in blood pressure as a primary endpoint, in the perspective of the impact on morbidity/mortality, but with reasonable objective since a too important blood pressure decrease is able to induce a deleterious effect. Parameters that are the domain of both medical and nursing care have been considered as secondary criteria. In the case of positive results, the CEOPS will constitute the basis of validated guidelines to optimize a multidomain intervention program for the follow up of patients after stroke, which is now a recommendation and a legal obligation in France. The preliminary descriptive analysis suggests a target population focused on younger patients with less severe stroke, which is the population needing optimal care to avoid recurrence and cognitive decline (Additional file 1).

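### The planned MoCA comparisons make no use of the discharge MoCA, so existing and new impairment are mixed; this does not bias the comparison but costs precision and may dilute a preventive effect

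*Protocol article*

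**What the plan says.** - Methods/design, Procedure: before discharge, "the quality of life scale and the Montreal Cognitive Assessment (MoCA) scale will be measured". A baseline value is therefore collected.
- Secondary outcomes: the outcome is "cognitive state by the MoCA scale".
- Analysis strategy: MoCA appears twice. It is among the "scores on different scales (Rankin, MoCA, EQ-5D" and so is compared by analysis of variance. It also appears as the "percentage of patients having a cognitive disorder (MoCA score <26". For such variables, "Qualitative data will be compared between the two groups based on the chi-squared test and calculation of odds ratios". No visit is named for either analysis, and no baseline covariate, change score or restriction on the discharge value is mentioned.
- Analysis strategy, on sub-groups: "Sub-group analyses will be planned secondarily, depending on the cause of the stroke or depending on the patient’s cognitive state". No time point is given for cognitive state.
- Participant eligibility, Table 1: severity is limited to "Patients who have had a stroke with sequelae allowing immediate return home or justifying a stay of less than 1 month in rehabilitation". There is no MoCA or other cognitive threshold.
- Discussion: the target population is described as one "which is the population needing optimal care to avoid recurrence and cognitive decline".

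**The concern.** The binary variable is a prevalence. Someone at 22 before discharge and still at 22 later is counted exactly like someone who fell from 28 to 22. The Background itself counts language, mood and cognitive problems among the hindrances to secondary prevention in these patients, so a discharge score below 26 should not be rare. If most of those deficits persist, they add cases to both arms that the programme did not change, and the odds ratio moves toward 1.

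The analysis of variance on the score has a related weakness. Discharge MoCA is likely to be among the best predictors of later MoCA, and leaving it out leaves avoidable variance in the comparison.

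The sub-group wording is a further loose end. Cognitive state is also the name of an outcome, so nothing in the text prevents the sub-group from being formed on a value measured after randomisation, which the programme could have affected.

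**Working it through.** **Inputs.** 205 patients per arm (Sample size consideration). That figure reproduces for the primary endpoint: 2 × (1.96 + 0.84)² × 18² / 5² gives 204 per arm, and the t-based calculation gives 204.4, hence 205. This works with 18 mmHg read as a standard deviation. No sample size or rate is stated for MoCA, so every MoCA rate below is an assumption.

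**1. No recovery among those already below 26.** Let p0 be the proportion below 26 at discharge. Let new impairment among the others be 20% (usual) and 10% (optimized). The proportion below 26 at the visit is p0 + (1 − p0) × incidence. At p0 = 50% this is 0.5 + 0.5 × 0.20 = 60% against 0.5 + 0.5 × 0.10 = 55%, and 0.50/0.60 = 83% of usual-arm cases were already cases at discharge. Power is the two-sided 5% normal approximation for two proportions, with no loss to follow-up. The new-impairment analysis uses 205 × (1 − p0) patients per arm and has an odds ratio of (0.10/0.90)/(0.20/0.80) = 0.44.

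| p0 | Below 26, usual vs optimized | Odds ratio | Power, all patients | Power, new impairment only |
|---|---|---|---|---|
| 20% | 36% vs 28% | 0.69 | 41% | 72% |
| 30% | 44% vs 37% | 0.75 | 30% | 66% |
| 50% | 60% vs 55% | 0.81 | 17% | 52% |
| 70% | 76% vs 73% | 0.85 | 10% | 34% |

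**2. Allowing recovery, at p0 = 50%.**
- Recovery 30% in both arms: 0.5 × 0.70 + 0.5 × 0.20 = 45% against 0.5 × 0.70 + 0.5 × 0.10 = 40%. Power is about 17%, so the dilution remains.
- Recovery 30% (usual) vs 40% (optimized): 45% against 0.5 × 0.60 + 0.5 × 0.10 = 35%. Power is about 54%, against 52% for new impairment only. At p0 = 70% the same assumptions give 55% vs 45% and about 53%, against 34%.

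**3. What the baseline adds in all patients.** As a simple stand-in for adjustment, stratify by discharge status (below 26 or not) and weight the strata by size. The variance of the risk difference is then the average within-stratum variance, and power is Φ(difference/SE − 1.96). At p0 = 50%:
- No recovery: SE = √[0.5 × (0.16 + 0.09)/205] = 0.0247; 0.05/0.0247 = 2.02; power about 53% (unadjusted 17%).
- Equal recovery: SE = √[{0.5 × (0.16 + 0.21) + 0.5 × (0.09 + 0.21)}/205] = √(0.335/205) = 0.0404; 0.05/0.0404 = 1.24; power about 23% (unadjusted 17%).
- Recovery 30% vs 40%: SE = √[{0.5 × (0.16 + 0.21) + 0.5 × (0.09 + 0.24)}/205] = √(0.35/205) = 0.0413; 0.10/0.0413 = 2.42; power about 68% (unadjusted 54%).

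Using the baseline helps in all three cases. Restricting to new impairment helps in the first two but not in the third.

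**4. The score.** Adjusting for a baseline with correlation ρ multiplies the variance of the arm difference by about 1 − ρ². With assumed ρ of 0.3, 0.5 and 0.7, that is 0.91, 0.75 and 0.51.

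**The case against.** A reader might infer that the percentage measures damage from the index stroke instead of later decline. The documents do not support that. Patients are randomised, so impairment present at discharge is balanced in expectation, and a difference between arms reflects what follows: new impairment or recovery. Chance imbalance is already in the standard error, and the type I error is unaffected.

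A reader might also infer that the trial cannot answer its own question about cognitive decline. Avoiding decline is a Discussion remark about the target population, not a stated objective. The secondary outcome is called cognitive state, which a percentage below 26 describes fairly. The score analysis would register a fall from 25 to 15 that the percentage misses.

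Nor does it follow that new impairment should replace the all-patient percentage. That changes the question and, if 30% to 70% are below 26 at discharge, drops 30% to 70% of patients. They include the cognitively affected patients whose difficulties motivate caregiver involvement. Its power advantage also vanishes once the programme is allowed to aid recovery.

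Finally, baseline adjustment, visit and sub-group timing for a secondary outcome are often left to the analysis plan, which is not shown and may already cover them. That tempers the point without removing it: the article does not leave the tests open but names them, and as named they are unadjusted. On the sub-group, the text does not say that a post-randomisation value will be used; it only fails to exclude it.

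**Conclusion.** The point holds as one of efficiency and clarity, not bias. As described, neither MoCA comparison uses a baseline that the trial collects, and the percentage mixes impairment present at discharge with impairment that arises later. If existing impairment mostly persists and the programme does not alter it, the odds ratio moves from 0.44 to between 0.69 and 0.85, and power falls to between 41% and 10%, for 20% to 70% below 26 at discharge. Those figures rest on assumed incidence of 20% vs 10% and no recovery. With recovery of 30% vs 40% and half below 26 at discharge, the all-patient percentage performs about as well as new impairment alone (54% vs 52%). The true size cannot be derived from the article. A secondary endpoint is affected; the primary blood-pressure result is not.

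**What to change.** - Name the visit for the MoCA comparisons.
- Compare the follow-up MoCA score in all patients by ANCOVA adjusted for discharge MoCA.
- Analyse MoCA below 26 in all patients by logistic regression adjusted for discharge MoCA. The adjusted odds ratio is conditional on baseline, so keep the raw percentages by arm beside it.
- Report new impairment among patients with MoCA of 26 or more at discharge as a supplementary result, not a replacement.
- Define the cognitive-state sub-group by discharge MoCA only.

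The cost is slightly more analysis work and a stated rule for patients without a discharge MoCA. No new data are needed. The article reports 215 of 410 patients recruited and no intermediate analysis, so the wording can be settled before any comparison between arms is seen. If the full analysis plan already provides this, confirming it is enough.

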## Methods/design

### Design

It will involve a controlled, randomized study comparing typical follow up, and a strategy of optimized patient follow up involving assigned nursing personnel in association with a caregiving member from the social circle. Patients who have had a stroke and meet the inclusion criteria will be randomized into two groups when they leave the hospital: (i) a group benefitting from optimized follow up for 2 years and (ii) a group of patients having typical follow up for 2 years (Fig. 1).

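### The named primary test (two-group ANOVA with Fisher PLSD) is valid but leaves out baseline systolic pressure and so gives up precision; the PLSD step adds nothing with two arms

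*Protocol article*

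**What the plan says.** The Primary outcome section sets the endpoint: "The main assessment criterion will be systolic blood pressure measured after the first year of follow up". The Analysis strategy section counts systolic pressure among the quantitative variables and gives one method for all of them: "Quantitative data will be compared between the two groups using analysis of variance", "with post-hoc analysis using Fisher’s least significant difference test in Prism (PLSD"). It mentions no covariate, no baseline value and no repeated-measures model.

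The Procedure section shows that starting values are collected: "Before being discharged, blood pressure, the abdominal perimeter, glycosylated hemoglobin, plasma concentrations of the various lipids", and then coagulation parameters, the Rankin score, quality of life and MoCA. Systolic pressure is measured again at 6, 12 and 24 months (Primary outcome).

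On timing, the Design section says that patients "will be randomized into two groups when they leave the hospital". The Procedure section mentions randomization first, then the two training sessions, and only then the measurements before discharge.

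The Sample size consideration section plans 205 patients per arm "to show a difference in systolic blood pressure of 5 mmHg", with alpha 5% and beta 20%. On the spread it says: "The variance in systolic blood pressure (18 mmHg) was calculated in the first 45 patients included in the study".

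**The concern.** A patient's starting blood pressure usually predicts later blood pressure to some degree. An analysis of variance with arm as the only factor leaves that predictable part in the residual. The standard error of the arm difference is then larger than it need be, and any chance difference in baseline pressure between the arms goes uncorrected.

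This matters because the trial has little margin. As the working shows, 205 per arm is just enough for 80% power with every patient measured at 12 months. The article gives no loss rate and shows no allowance for loss, although it cites the risk of losing patients when it justifies the one-year time point.

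The PLSD step is a smaller matter. Fisher's least significant difference follows a significant F test when three or more groups are compared in pairs. With two arms there is one pair, and its LSD test is the F test itself. The step therefore adds no information and leaves the reader unsure which model is meant.

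**Working it through.** **Inputs from the protocol article (Sample size consideration):** difference 5 mmHg; spread 18 mmHg; alpha 5%; power 80%; 205 per arm. The 18 is called a variance, but its unit is mmHg and the stated sample size reproduces only if it is a standard deviation (read as a variance, it gives 12 per arm). Alpha is taken as two-sided, since one-sided would give 161 per arm.

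**Inputs not in the article (assumptions):** correlation r between baseline and 12-month systolic pressure, 0.1 to 0.5; loss before 12 months, 0% or 10%.

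**Step 1. Reproduce the stated size.** Normal approximation: n per arm = 2 × (1.960 + 0.842)² × 18² / 5² = 203.5, so 204. With the noncentral t distribution, 204 per arm gives 79.9% power and 205 gives 80.1%, so 205 per arm (410 in total) is reproduced exactly. It uses the full SD, with no reduction for baseline correlation and no allowance for loss. The sample size and the unadjusted test therefore agree.

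**Step 2. Effect of baseline adjustment.** ANCOVA residual SD = 18 × √(1 − r²). Noncentrality = 5 / (residual SD × √(2/n)), with 2n − 2 degrees of freedom. (The one degree of freedom spent on the covariate is ignored, which is immaterial at this size.) Example at r = 0.5, n = 205: residual SD = 18 × √0.75 = 15.59; noncentrality = 5 / (15.59 × √(2/205)) = 3.25; power 90.0%. Unadjusted: 5 / (18 × √(2/205)) = 2.81; power 80.1%.

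| Assumed r | Residual SD (mmHg) | Power, 205 per arm | Power, 10% loss (184.5 per arm) |
|---|---|---|---|
| unadjusted | 18.00 | 80.1% | 75.8% |
| 0.1 | 17.91 | 80.5% | 76.3% |
| 0.2 | 17.64 | 81.7% | 77.5% |
| 0.3 | 17.17 | 83.7% | 79.7% |
| 0.4 | 16.50 | 86.5% | 82.7% |
| 0.5 | 15.59 | 90.0% | 86.7% |

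**Step 3. Change score as an alternative.** A change from baseline has SD 18 × √(2(1 − r)) if both readings have SD 18. At r = 0.3 this is 21.3 mmHg and power drops to about 66%. At r = 0.5 it equals the unadjusted test. Below r = 0.5 a change score does worse than no adjustment, so baseline should enter as a covariate.

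**Step 4. Is the pre-discharge reading a safe covariate?** Design places randomization at the time of leaving hospital, which would put the pre-discharge reading before it. Procedure describes randomization and the training sessions ahead of those measurements. The article does not settle the order. A reading taken after randomization and training could already carry some of the intervention's effect, and adjusting for it could remove part of that effect from the estimate.

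**The case against.** The strongest reply is that nothing here is an error. Under randomization the unadjusted comparison is unbiased and keeps its type I error, its standard error already allows for chance imbalance, and it matches the sample size. All of that stands. A reader might infer that the planned test is biased or that the trial is underpowered as designed; the documents support neither.

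A second reply is that covariates are commonly left to the statistical analysis plan, which is not shown, and that the sentence is a generic one covering all quantitative variables. This carries some weight. But the article names a specific test, down to the post-hoc procedure, so a plan that added baseline would depart from the published method. One could also read the PLSD step as a sign of a wider ANOVA with visit as a factor. That is possible, but the sentence speaks of comparing two groups and the article names no such factor.

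Third, the gain may be small. The covariate is an in-hospital reading after a stroke, and Table 1 admits patients whose hypertension was discovered at the stroke and who are only starting treatment. A low r is plausible, and at r = 0.1 the gain is under half a point. This stands, and it is why the range starts there.

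Two further inferences are tempting and should not be drawn. The article does not say that patients without a 12-month value are dropped; it is silent on missing data. Nor does it follow that every continuous secondary endpoint gains as much, since each gain depends on that variable's own correlation, which is not given.

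**Conclusion.** The point holds as one of efficiency. The named primary comparison is valid and consistent with the sample size, but it leaves out a baseline measurement that the trial already takes. In power, the cost of leaving it out runs from 0.4 percentage points (r = 0.1) to about 10 (r = 0.5) with complete follow-up, and from 0.5 to about 11 with 10% loss. At that loss, adjustment brings power back to about 80% or more only if r is roughly 0.3 or higher. These figures rest on an assumed correlation, an assumed loss rate and the article's SD of 18 mmHg. That PLSD is redundant for two arms needs no assumption. The change should be made, but the trial's validity does not depend on it.

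**What to change.** Replace the analysis-of-variance and PLSD sentence as follows.

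- **Primary analysis:** ANCOVA of 12-month systolic pressure with arm and baseline systolic pressure as terms. Alternatively, a mixed model for repeated measures on months 6, 12 and 24 with arm-by-visit and baseline-by-visit terms, taking the single arm contrast at month 12. Choose one in advance and report the adjusted mean difference with its 95% confidence interval.
- **Baseline definition:** state that the covariate is a reading taken before randomization and before the training sessions, and reconcile the order of events between Design and Procedure.
- **Continuous secondary endpoints:** adjust in the same way where a pre-randomization value of the same variable exists.
- **PLSD:** delete it for the two-arm comparison.

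The cost is a wording change in the analysis text, plus a check that blood pressure was in fact recorded before randomization. If it was, no new data are needed. The article reports no interim analysis and 215 of 410 patients recruited, so on that status the change can be fixed before any comparison of the arms.
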